## 2) OBJECTIVES

*The primary objective* of this study is to evaluate effects of gamification and format of survey administration on participant retention, compliance, and engagement in a 6-month longitudinal study. The study will be structured as a siteless trial, in which brief (2-10 min) surveys will be administered remotely once per week in paper or electronic format.

To evaluate the primary objective, each participant will be assigned to one of four Arms, each consisting of two cohorts which will be recruited in sequence. Participants in each arm receive the surveys in a different format during the study (see table below). Participants in the cohorts will receive the same total compensation but on a different schedule. After enrolling approximately 50 participants each into the rapid payment cohorts (once every two weeks) of arms A, B, C, and D, or approximately 200 participants total, enrollment into the delayed payment cohorts (lump sum after 6 months) will begin.

| Arm   | Format of survey administration      | Gamified format?                                                                      | N (Approximate) | Payment Schedule                             |
|-------|--------------------------------------|---------------------------------------------------------------------------------------|-----------------|----------------------------------------------|
| Arm A | Electronic: Smartphone app           | Yes (opportunity to earn points, create custom avatar, track study progress on a map) | 50              | \$5 per completed survey, paid every 2 weeks |
|       |                                      |                                                                                       | 50              | \$5 per completed survey paid at 6 months    |
| Arm B | Electronic: Datacubed Health website | No                                                                                    | 50              | \$5 per completed survey, paid every 2 weeks |
|       |                                      |                                                                                       | 50              | \$5 per completed survey paid at 6 months    |
| Arm C | Non-electronic: Paper                | No                                                                                    | 50              | \$5 per completed survey, paid every 2 weeks |

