|       |                                      |                                                                                       | 50              | \$5 per completed survey paid at 6 months    |
| Arm D | Electronic: Third-Party website      | No                                                                                    | 50              | \$5 per completed survey, paid every 2 weeks |
|       |                                      |                                                                                       | 50              | \$5 per completed survey paid at 6 months    |

*The secondary objective* of the study is to assess the effect of gamification on participant satisfaction when performing cognitive tasks, as opposed to surveys. Participants who complete any of the initial 6-month cohorts will be recontacted and asked if they would like to continue into an optional, two-week follow-up period. Up to 400 participants will be recruited for this objective. Participants will then be re-randomized in the follow-up period. Participants will be

assigned (1:1) to one of two Arms, E and F. Arm E will examine participant satisfaction with non-gamified, web-based cognitive tasks. Arm F will examine participant satisfaction with gamified, app-based cognitive tasks. Satisfaction will be assessed using a standard, validated instrument, the Technology Acceptance Model (TAM) questionnaire delivered by web or app. Participants will receive \$5 for each completed task or survey after the two-week follow-up period is complete, or up to \$30 in compensation.

| Arm   | Format of task administration | Gamified format?                                                                      | N (Approximate) |
|-------|-------------------------------|---------------------------------------------------------------------------------------|-----------------|
| Arm E | Electronic: Smartphone app    | Yes (opportunity to earn points, create custom avatar, track study progress on a map) | Up to 200       |
| Arm F | Electronic: website           | No (interactive, web-based tasks)                                                     | Up to 200       |

The specific aims of the study are:

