#### **5) STUDY-WIDE NUMBER OF SUBJECTS**

We plan to enroll up to 400 individuals in the study (see Section 9).

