## 9) STUDY DESIGN AND PROCEDURES

### Arms A-D

This study will employ at initial recruitment a between-subjects design with four, independent arms, divided into two sequential cohorts.

Each participant will first complete the informed consent process (see Section 29). Upon receipt of the signed consent (signature captured digitally), Datacubed Health will assign the participant

to one of 4 groups; group assignment will determine the medium through which the surveys will be administered -- gamified mobile app (Arm A), web browser (Arm B & Arm D), or paper (Arm C). Approximately 100 participants are expected to be enrolled into each group.

Group assignment will be done sequentially by date and time of consent signature – i.e., the first participant who signs consent will be assigned to Arm A; the second participant, to Arm B; the third participant, to Arm C; the fourth participant, to Arm D; the fifth participant, to Arm A; the sixth participant, to Arm B; etc. The first cohort of participants recruited into each arm will receive compensation every two weeks based on how many instruments they complete (\$5/instrument). The second cohort of participants recruited into each arm will receive a single payment at the conclusion of the 6-month arm. Compensation will be the same, \$5/instrument, but delivered as a single lump sum payment after completion. The maximum, total compensation possible in the initial 6-month study period will be \$130.

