## **29) CONSENT PROCESS**

Written consent will be obtained for this study. Potential participants who are interested in the study and who have met study eligibility criteria will be asked to provide consent electronically via Datacubed Health's secure, HIPAA-compliant web-based platform.

For each participant, the following steps for the consent process will be followed:

- One of the study investigators (PI or Sub-Is) will add the participant to Datacubed Health's database by entering the name and email address of the participant.
- The Datacubed Health database will generate and send an email to the participant containing a link to the secure web platform and unique temporary log-in credentials.
- Using the link and temporary log-in credentials received by email, the participant will log into the web platform. The participant will update his/her password and will then be prompted to review the study consent form.
- The participant will be able to read the consent form in its entirety. To facilitate understanding and comprehension, a short summary of certain sections will be provided to re-iterate important points in succinct, clear language.
- The consent form will contain contact information for Datacubed Health (email and phone number). If the participant has any questions or concerns as a result of reviewing the consent form, he/she can contact Datacubed Health to further discuss before signing the consent form. One of the study investigators (PI or Sub-Is) will contact the participant within 1-2 business days to discuss the participant's questions or concerns directly.
- After the participant has read the consent form, the participant will need to answer several comprehension questions (see separate attachment) to ensure that he/she has

understood the form and is able to give informed consent. If the participant answers all comprehension questions correctly, he/she will be given the opportunity to sign the consent form. If a participant does not answer the comprehension questions correctly, he/she will be redirected back to review the consent form content, then will have the opportunity to complete the comprehension questions again. This process will be repeated such that each participant will have a total of 3 chances to correctly complete the comprehension questions. If the participant is unable to correctly complete the comprehension questions after 3 attempts, the participant will be removed from consideration for the study.

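### Arms A-D are filled by a fixed A-B-C-D rotation in order of consent, with no random element or concealment, so the next signer's arm is always known to anyone holding the running count.

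*Protocol*

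**What the plan says.** Section 9 (Arms A-D) sets the rule: "Group assignment will be done sequentially by date and time of consent signature". It spells out the order, "the first participant who signs consent will be assigned to Arm A; the second participant, to Arm B", and shows the cycle restarting: "the fifth participant, to Arm A; the sixth participant, to Arm B". The section calls this assignment within a between-subjects design and does not call it randomisation. Each participant learns the assignment at once.

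The steps before signature involve the sponsor's staff. Under Section 6 the study team invites those whose screening answers meet the criteria. Under Section 29, "One of the study investigators (PI or Sub-Is) will add the participant to" the database, which sends the consent e-mail. An investigator also contacts any candidate who raises questions before signing. Section 21 says that the whole research team took part in designing the study and has access to the protocol.

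The secondary objective in Section 2, on the optional follow-up, says: "Participants will then be re-randomized in the follow-up period". Arms E and F are the only arms that the protocol describes as randomised.

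In Section 11, Aims 1 to 4 compare the arms by analysis of variance with no covariates named. For Aims 1 and 2, confounding is said to be dealt with by leaving one arm out. Section 9 plans to examine whether demographics are associated with the outcomes, but does not say that the arm comparisons will be adjusted for them.

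**The concern.** Random, concealed allocation lets a difference between arms be attributed to the survey format rather than to who was put in each arm. A fixed rotation supplies neither the randomness nor the concealment. The sponsor makes the assignments, so the running count is available in-house, and the rule is in a protocol that the whole team can read.

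The interest is not neutral. Arm A is the sponsor's app and Arm B its website, and the hypotheses favour them over paper and, for usability, over the third-party site. The outcomes are retention, compliance and usability. A candidate's responsiveness before consent plausibly predicts the first two. Staff can see that responsiveness in correspondence, and Section 29 asks the sponsor to assess it as part of eligibility review.

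If invitations or replies were timed with the next arm in mind, more responsive people could collect in some arms. Aims 1 to 3 and the format factor of Aim 4 all depend on the arms being comparable. The allocation cannot be repaired after enrolment, and a result favouring the sponsor's product would meet a selection objection that the design could not answer.

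**Working it through.** **Inputs.** Rotation order and about 100 per arm (Section 9); up to 400 in total (Section 5); about 200 enrolled before the second payment cohort opens (Section 2). The protocol gives no alpha, power or effect size, and none is needed here.

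**Step 1: the stated sizes.** Rotation over 400 consents gives 400 / 4 = 100 per arm. The first 200 give 200 / 4 = 50 per arm, and so do the second 200. This matches "Approximately 100 participants are expected to be enrolled into each group" and the cohorts of about 50. The rotation does deliver the planned balance.

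**Step 2: what fixes the arm.** For signer k, take the remainder of k divided by 4: 1 gives A, 2 gives B, 3 gives C, 0 gives D. Signer 5 has remainder 1 (A) and signer 6 has remainder 2 (B), as the protocol states. Nothing else enters.

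**Step 3: predictability.** The measure is the share of assignments guessed correctly by someone who knows the scheme and all past assignments.

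| Scheme (1:1:1:1) | Calculation | Correct guesses |
|---|---|---|
| Rotation, as written | arm fixed by k | 100% |
| Permuted blocks of 4, size known | (1/4)(1/4 + 1/3 + 1/2 + 1) = 2.083 / 4 | 52.1% |
| Permuted blocks of 8, size known | simulation, 50,000 blocks | about 47% |
| Permuted blocks of 12, size known | simulation, 50,000 blocks | about 44% |
| Simple randomisation | 1/4 | 25% |

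If blocks of 4 and 8 are mixed, someone told every block size would be right between about 47% and 52% of the time. Someone not told the sizes could do no better.

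**Step 4: what the 100% refers to.** It applies to the next person to sign, not to a chosen candidate. After being entered, a candidate receives an e-mail, logs in, reads the form, passes comprehension questions (up to three attempts) and then signs. With several invitations open at once, staff cannot tell which position in the sequence a given invitee will take. Steering would need paced invitations or well-timed replies to questions.

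**Step 5: the wording.** Section 9 describes a rotation for A-D. The Section 2 sentence on the follow-up presupposes that A-D had been randomised. Both cannot be right as they stand.

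**The case against.** Four points on the other side deserve weight.

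First, a reader might infer that the protocol presents Arms A-D as randomised. It does not. Section 9 discloses the rotation openly and Section 11 never invokes randomisation. The only support is one prefix in a sentence about Arms E and F. This stands: that part of the point is a wording conflict, not a false claim about the design.

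Second, a reader might take 100% predictability to mean that staff can place any candidate in any arm. Step 4 of the working shows why the documents do not support that. The protocol also does not say that invitations go out singly, or that every investigator sees the live count.

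Third, the protocol contains mitigating features. Section 6 describes inviting those who meet the criteria, without a discretionary choice. Section 21 calls the criteria broad and enrolment largely automated. Contact before signature happens only if the candidate has questions, and participants have no evident way to know the count. Nothing suggests that position in a cycle of four is itself related to retention. All of this lowers the likelihood of bias, but none of it supplies concealment.

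Fourth, a reader might conclude that the analysis-of-variance, Dunnett and Tukey p-values have no basis. That goes too far: such tests can rest on a sampling model and do not strictly require random allocation. What is at risk is the comparability of the arms.

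**Conclusion.** The point holds as a design weakness that is easily avoided. Allocation to Arms A-D is deterministic and unconcealed. The next signer's arm is known with certainty to anyone with the running count, about twice the 52% rate of known blocks of 4 and four times the 25% of simple randomisation. These rates measure predictability, not harm.

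The documents show an opportunity for selection, through the timing of invitations or of contact before signature, by staff of a company whose products are two of the four arms. They do not show that selection occurs, and they give nothing from which its size could be bounded.

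The conclusion assumes that at least some of the staff who invite or talk with candidates can learn the count. The protocol does not say so, but nothing in it prevents this. The conflict between Sections 2 and 9 is a separate, minor matter of wording. The sequential payment cohorts of Aim 4 raise a different question, which is not part of this point.

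**What to change.** **Preferred.** In Section 9, replace the rotation with a computer-generated permuted-block list for 1:1:1:1 allocation with varying block sizes, for example 4 and 8. Conceal the list from all staff who invite or talk with candidates. Let the platform apply the next entry once the signature is stored. Assignment already follows receipt of the signed consent, so what is new is the random list and its concealment. The Section 2 wording on the follow-up then becomes correct without change.

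**If the rotation is kept.** Describe it in Section 9 as systematic, non-random allocation. Change the Section 2 sentence so that the follow-up is the first randomisation, not a second. In Section 11, adjust the arm comparisons for the demographics that Section 9 already collects from everyone. This is the weaker option, because adjustment cannot deal with unmeasured traits such as responsiveness.

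**Cost.** The preferred option needs one rewritten paragraph and a generated list, with no extra participants or staff. Balance is kept: in blocks of 8 each arm appears twice, so stopping part-way through a block leaves any two arms at most two participants apart, and the arms stay at about 50 per cohort and about 100 overall. The change must be made before the first participant is assigned.

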### **Arms E and F**

At the end of the initial 6-month participation period, all participants will be asked if they would like to continue into an optional two-week, follow-up period. At the end of this period, participants will be asked if they would like to be contacted about other research opportunities. Participants who complete PEARL study measures, and agree to be contacted, may be contacted in the future, via email, as part of recruitment efforts for other projects.

## **10) DATA AND SPECIMEN BANKING**

No specimens will be collected in this study.

When the study ends and we close out the study with the IRB, we will purge all personally identifiable data except location data (see section 26). While we may use the resulting deidentified data for internal product development purposes, we do not plan to release the data; access to the deidentified data will remain limited to members of Datacubed Health who have received CITI training in the handling of human subjects data. We will never release personally identifiable information (including raw location data) outside the organization.

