Certain demographic data, such as age (month and year of birth only; all subjects are under 90), gender, sex, ethnicity, education level, employment status, annual income level, and type of smartphone, will be collected from all participants. These data will be analyzed to see if they are associated with any differences in retention, compliance, and engagement. For security, these data will be encrypted and stored in separate files, which can only be referenced through the anonymous subject ID that is assigned to each participant for the study.

Survey data, including survey responses, number of surveys completed, and dates of survey completed will be collected for all participants. These data will be used to evaluate the study endpoints of participant retention, compliance, and usability.

In addition to the aforementioned data types, for the group assigned to the gamified mobile app, several types of data provided by the phone operating system will be collected:

- **Passive data:** These types of data will be collected even when the participant is not actively using the app. Specifically, the app will record information about the participant's

phone battery percentage, geolocation, number of steps taken, apps installed on the phone, and phone screen on/off times. Participants will be fully informed during the consent process that the app will collect such data. They will be able to disable collection of location and step count data at any time by restricting the app permissions via the phone operating system; Android phone owners will also be able to restrict permissions for data collection on screen time.

- Geolocation is the collection of precise geographical location (latitude and longitude) of a device through a mixture of GPS and WiFi signals. This technology is used by many other apps that provide services based on a user's location, such as navigation, rideshare, banking, dating, and fitness apps. When location permissions are allowed, location data is sent to the app every few minutes. In this study, geolocation data will only be used to develop a data-driven model of participants' daily routines. This model will then be compared with self-reported measures of daily activity to see if geolocation data can serve as a measure of activity and routine. Datacubed Health will not share geolocation data with any other external parties and will destroy this data at the end of the study.

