## **14) RISKS TO SUBJECTS**

We do not anticipate any direct physical risks to the participant.

Risks to the subjects are minimal and do not exceed those encountered in daily life. Subjects may experience eye strain normally associated with reading and writing. Subjects will be informed that if they experience any discomfort of this kind they should cease the activity and rest before returning to the study-related task.

Participants may experience some psychological discomfort when answering survey questions that ask about thoughts, mood, or behaviors. Subjects are free not to answer any questions that they find uncomfortable.

The primary risk associated with this study is that an unauthorized party could gain access to study data and use it to identify participants. However, we have taken many precautions to ensure that this will not happen. The software systems we will use are built to protect the security of sensitive study data (see Sections 11 and 25). We will use safeguards such as strong encryption for all data on participants' phones, in transit to our servers, and on our servers. All access to study data will be password-protected and limited to authorized members of the study team. Other personnel involved in the development and maintenance of the software (e.g. the server administrator) will only have access to non-sensitive metadata (e.g. information about the date and time of failed data transmissions). Although we will do everything in our power to ensure the continued privacy and security of data from the study, unauthorized or unintentional disclosure of such data remains a minimal risk.

Geolocation data can also carry privacy risks for participants when the use, sharing, and handling of location data are not fully disclosed to participants. During the consent process, participants will be informed that the only use of geolocation data in this study is for comparison with self-reported survey data (i.e., to determine whether geolocation could serve as a novel measure of activity and routine); that the data will not be shared with any external parties; and that the data will be destroyed at the end of the study. Geolocation data will be handled in the same manner as PII.

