## **26) PROVISIONS TO PROTECT THE PRIVACY INTERESTS OF SUBJECTS**

Research data will be coded, access-protected, and encrypted both at rest and in transit to ensure data privacy and security (see Section 11 - Data Management for details).

Some personally identifiable information (PII) such as name, email address and phone number must be collected from participants during the screening process for administrative purposes: this information will enable us to contact the participant when necessary and to enable reimbursement payments. This PII will not be directly linked to research data about the participants on the server, and the coded data will never be linked to these PII during data analysis. A table linking PII to participants' coded IDs will be kept in a separate encrypted and password-protected database that will only be accessible to study personnel. At the conclusion of the study, when the closure of the study is approved by the IRB, we will permanently delete the table containing the administrative PII.

Throughout the entire study, and after, we will also take additional precautions to ensure that geolocation data collected by the app cannot be used to identify participants. We will never publish nor otherwise disseminate raw geolocation data. We will only publish or otherwise disseminate geolocation data that is not identifiable (e.g. short snippets of data that are not linked to a particular date and time, or summary data that are aggregated over time and/or participants).

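### Section 10 exempts location data from the end-of-study purge, but Section 9 says the data will be destroyed and Section 14 says participants will be told so

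*Protocol*

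**What the plan says.** Five sections of the protocol bear on what happens to Arm A location data.

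- **Section 10 (Data and Specimen Banking).** At close-out, "we will purge all personally identifiable data except location data", with a reference to Section 26. It then says that "we may use the resulting deidentified data for internal product development purposes", with access limited to trained staff of the sponsor. It ends: "We will never release personally identifiable information (including raw location data) outside the organization".
- **Section 9 (Arms A-D, passive data).** "Datacubed Health will not share geolocation data with any other external parties and will destroy this data at the end of the study". It limits use in this study to a model of daily routines, which is then compared with self-report. Earlier in the section, administrative identifying information is also to be destroyed at study end.
- **Section 14 (Risks to Subjects).** During consent, participants will be informed that "the only use of geolocation data in this study is for comparison with self-reported survey data", that nothing goes to external parties, and that the data will be destroyed when the study ends. Geolocation is to be treated in the same way as identifying information.
- **Section 11 (Data Management).** De-identification means removing ID codes. The section concedes that geolocation may identify a person by itself. It also says that data stay on the server for the length of the study.
- **Section 26 (privacy provisions).** The table of administrative identifiers is deleted at closure. Raw geolocation data are never published, but non-identifiable extracts may be, for example "short snippets of data that are not linked to a particular date and time".

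**The concern.** Whoever closes out the study must either delete the location data or keep them, and the protocol gives both instructions. The conflict goes beyond tidiness because Section 14 fixes what participants are told when they consent. Someone who leaves location permissions on does so after being told that the traces will be destroyed.

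Section 14 names, as the primary risk, an unauthorized party gaining access to study data and identifying participants. It calls that risk minimal. Keeping precise location data after closure prolongs the exposure for the data type that Section 11 singles out as possibly identifying in itself.

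A second, smaller question follows. If location data survive the purge, the protocol does not say clearly whether they may be used for product development.

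**Working it through.** No figure in the protocol is in dispute and no power or error-rate calculation applies. The check sets the statements side by side.

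**1. Keep or destroy**

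| Section | Fate of location data at study end |
|---|---|
| 9 | Destroyed |
| 14 | Participants told it is destroyed; handled like identifying information, which Section 9 says is destroyed |
| 11 | Server data kept for the duration of the study |
| 10 | Exempt from the purge |
| 26 | Not stated; only the administrative identifier table is deleted |

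Sections 9 and 14 agree with each other, and Section 11 fits them. Section 10 makes location data the one exception among identifiable data, which is the opposite of treating it like the rest. Section 26 says that precautions for geolocation continue after the study. That would fit retention, but it neither orders retention nor rules out destruction. The cross-reference therefore does not resolve the conflict.

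**2. Use of what remains**

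Section 10 opens product development to the deidentified data that result from the purge. Two readings are possible.

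- *Location data included.* The purge spares location data, and Section 11 defines de-identification as removal of ID codes. Location traces without ID codes would then qualify.
- *Location data excluded.* The last sentence of Section 10 counts raw location data as personally identifiable, so they would not be deidentified data.

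The text does not choose between them. Under the first reading, Section 10 would sit badly with the single use stated in Section 9 ("geolocation data will only be used to develop a data-driven model of" daily routines) and in Section 14.

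**3. Sharing**

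Sections 9 and 14 say without qualification that geolocation data are not shared externally. Section 26 allows dissemination of non-identifiable extracts and summaries. The statements differ in scope. Publishing such extracts is compatible with destroying the raw data, so this is a matter of alignment and not a second contradiction about destruction.

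**4. Who is affected**

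Arm A has two cohorts of about 50, and 50 + 50 = about 100. Section 9 says location data are sent only when permissions are allowed and that participants can switch them off at any time. About 100 is therefore an upper bound.

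**The case against.** The best defence is that the exception in Section 10 is a stray remnant. Sections 9, 11 and 14 point one way, and Section 10 itself bars release of raw location data outside the organization and restricts access to trained staff. That makes it likely which statement is the outlier. It does not remove the conflict, because no text gives one section precedence and Section 10 is where the close-out rule stands.

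A reader might infer several stronger points that the protocol does not support.

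- *That the sponsor plans to use location data for product development.* Section 10 does not name location data in that sentence, and the single-use statements are limited to use in this study. The wording is ambiguous and no more can be said.
- *That Section 26 permits publication of location snippets during and after the study.* Its reference to the time during and after the study governs the precautions. The publication sentence is separate and restrictive.
- *That none of these rules can be followed together.* Only keeping and destroying exclude each other. Product use is optional, and Section 26 limits what may be disseminated.
- *That continuous six-month traces exist for everyone in Arm A.* Collection depends on permissions. Section 9 adds that most operating systems stop sharing location in battery-save mode or after a period without app use.
- *That the lawfulness of the Exploratory Aim 2 analysis is in doubt.* Nothing in the protocol supports this. That analysis is the use which Sections 9 and 14 describe.

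**Conclusion.** The contradiction between Section 10 and Sections 9 and 14 stands on the wording alone. If Section 10 is followed, the statement about destruction made at consent is broken for Arm A participants who allow location collection, at most about 100. Whether retained location data could go to product development is unclear, and the mismatch on sharing is minor.

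The point should be corrected, but it has no bearing on the analyses of Aims 1 to 5. The conclusion rests on two assumptions. The first is that the consent information says what Section 14 says it will, since the form itself is not available here. The second is that location is collected only in Arm A, because the protocol does not say whether the app used in the two-week follow-up also records it.

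**What to change.** Reconcile the sections before participants consent, by one of two routes.

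1. Remove the exception for location data from the purge sentence in Section 10, and add that raw location data are excluded from product-development use. Section 10 then matches Sections 9 and 14.
2. If retention is intended, change Sections 9 and 14 and the consent information so that participants are told before consent that location data are kept and how they may be used.

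Under either route, qualify the no-sharing statements in Sections 9 and 14 so that they agree with Section 26 on non-identifiable extracts. Section 26 need not be narrowed to remove the contradiction.

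The first route costs a few words and gives up later reuse of raw location data. The second keeps that option, at the cost of revising the consent information as well as the protocol.
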